**Methods:**

An investigator-initiated, open label, randomized controlled trial, set in a general ICU specialized in liver disease, was initiated in August 2022, with an expected duration of 36 months. Seventy patients with cirrhosis and ascites will be randomly assigned, in a 1:1 ratio, to receive one of two methods of therapeutic paracentesis. A stratified randomization method, with maximum creatinine and IAP values as strata, will homogenize patient baseline characteristics before trial group allocation, within 24 h of admission.

In the control group, LVP will be performed intermittently according to clinical practice, with a maximum duration of 8 h, while, in the intervention group, continuous passive paracentesis will drain ascitic fluid for up to 7 days.

The primary endpoint is serum creatinine concentration, and secondary endpoints include IAP, measured creatinine clearance, daily urine output, stage 3 acute kidney injury and multiorgan dysfunction assessed at day 7 after enrollment, as well as 28-day mortality rate and renal replacement therapy-free days, and length-of-stay. Prespecified values will be used in case of renal replacement therapy or, beforehand ICU discharge, liver transplant and death. Safety analysis will include paracentesis-related complication rate and harm. Data will be analyzed with an intention-to-treat approach.

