### Outcomes {12}

The primary outcome is serum creatinine concentration. The secondary outcomes are IAP, measured creatinine clearance, daily urine output, the multiorgan disfunction score Chronic Liver Failure Sequential Organ Failure Assessment (CLIF-SOFA) [13] and the incidence of stage 3 acute kidney injury (AKI) (defined by Kidney Disease: Improving Global Outcomes—KDIGO AKI [29] score), as well as 28-day renal replacement therapy (RRT)-free days, 28-day survival rate, and ICU LOS. The outcomes variables will be assessed at day seven (D7) after randomization (D0), unless otherwise stated. Additionally, IAP, serum creatinine concentration, measured creatinine clearance, daily urine output, and CLIF-SOFA will be analyzed using their maximum or minimum and daily mean values between D1 and D7.

Whenever ICU discharge or liver transplant occurs before D7, the last available data prior to these events will be used for outcome assessment. Additionally, stage 3 AKI will be considered when RRT or death occurs and, in these circumstances, a serum creatinine concentration value of 4 mg/dL and creatinine clearance value of 10 mL/min will be used for outcome assessment as mentioned in the literature [13, 29, 30].

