## Statistical methods

### Statistical methods for primary and secondary outcomes {20a}

For the descriptive analysis, quantitative variables will be reported as means and standard deviations or as medians and interquartile ranges (*P*_25_-*P*_75_), as appropriate, and categorical variables reported as frequencies and percentages.

Quantitative variables will be analyzed using the assessment day value (D7), the daily mean value, and their maximum or minimum values. Mann–Whitney *U* test will be used to compare study groups, assuming a non-normal distribution, or two independent sample *t*-test, in case of normal distribution. Dichotomous categorical variables will be analyzed using chi-square or Fisher’s exact tests. Using daily values, mixed effects regression models will be used to consider the autocorrelation structure between the longitudinal measurements. Regarding stage 3 AKI as secondary outcome, odds ratios and corresponding 95% confidence intervals will be estimated using logistic regression models. For the study of RRT-free days, competing risks survival models will be applied considering death as the competing risk. Regarding time until death, joint survival regression models will be used to take into consideration the association of longitudinal markers with time until death. For LOS, linear regression models will be applied. For all regression studies, univariable and multivariable analyses will be performed to account for potential confounders. The absolute risk of paracentesis-related complications will be reported for both trial groups. A level of significance *α*= 0.05 will be considered. Data will be analyzed using the R Statistical Software [41].

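### The secondary outcome named incidence of stage 3 AKI also counts every death by D7, so its odds ratio describes AKI, RRT or death, not AKI alone

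*Protocol article*

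**What the plan says.** Under Outcomes {12}, the protocol article lists as a secondary outcome "the incidence of stage 3 acute kidney injury (AKI) (defined by Kidney Disease: Improving Global Outcomes—KDIGO AKI [29] score". The next paragraph of that section sets the counting rule: "stage 3 AKI will be considered when RRT or death occurs". In the same circumstances "a serum creatinine concentration value of 4 mg/dL and creatinine clearance value of 10 mL/min will be used for outcome assessment". The timing default in the section is "The outcomes variables will be assessed at day seven (D7) after randomization (D0), unless otherwise stated".

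The abstract (Methods) lists the endpoint as "stage 3 acute kidney injury and multiorgan dysfunction assessed at day 7 after enrollment" and adds that "Prespecified values will be used in case of renal replacement therapy or, beforehand ICU discharge, liver transplant and death". It does not say that a death becomes an AKI event.

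Under Statistical methods {20a}: "Regarding stage 3 AKI as secondary outcome, odds ratios and corresponding 95% confidence intervals will be estimated using logistic regression models". The same paragraph treats death differently for another renal outcome: "For the study of RRT-free days, competing risks survival models will be applied considering death as the competing risk". Survival to 28 days is a separate secondary outcome.

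**The concern.** The name and the counting rule describe different variables. By name and definition the outcome is a KDIGO renal stage. By the rule, a patient who dies by D7 with preserved renal function is recorded as having stage 3 AKI.

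Such patients can occur in this trial. Two of the four stratification subgroups have a maximum creatinine below 1.5 mg/dL, so patients without marked renal dysfunction are expected. The Discussion also gives reasons why non-renal deaths might differ between arms: the continuous strategy may lower the risk of perforation and bleeding, but may raise the risk of infection. These act in opposite directions, so the direction of any distortion cannot be foreseen.

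At stake is the reading of the result. An odds ratio published for stage 3 AKI will be taken as evidence about the kidney, which is the trial's main target. It could point to a renal benefit or harm that the renal data do not show, or conceal one that they do.

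**Working it through.** **Figures in the plan.** The document gives no event rate, odds ratio or power for stage 3 AKI, so there is no stated figure to reproduce. The only input taken from it is the total of 70 patients at 1:1, that is 35 per arm. The sample size calculation for creatinine is not affected by this point. All rates below are assumptions.

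**Formula.** Let *a* be the risk of true stage 3 AKI or RRT by D7, and *d* the risk of death by D7 among patients otherwise free of it. The recorded risk is *p* = *a* + (1 − *a*) × *d*. The odds ratio is [*p*₁/(1 − *p*₁)] / [*p*₀/(1 − *p*₀)].

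**Apparent effect with no renal difference.** Take *a* = 0.25 in both arms, so the true AKI odds ratio is 1.0.

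- *d* = 0.05: *p* = 0.25 + 0.75 × 0.05 = 0.2875, odds 0.2875/0.7125 = 0.4035
- *d* = 0.15: *p* = 0.25 + 0.75 × 0.15 = 0.3625, odds 0.3625/0.6375 = 0.5686
- *d* = 0.20: *p* = 0.25 + 0.75 × 0.20 = 0.40, odds 0.40/0.60 = 0.6667

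The arm with more deaths against the arm with fewer:

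- 15% vs 5%: OR = 0.5686/0.4035 = 1.41
- 20% vs 5%: OR = 0.6667/0.4035 = 1.65

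**Precision at 35 per arm.** Expected events are 0.2875 × 35 = 10.06, 0.3625 × 35 = 12.69 and 0.40 × 35 = 14.

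- 15% vs 5%: SE of log OR = √(1/10.06 + 1/24.94 + 1/12.69 + 1/22.31) = 0.513, 95% CI about 0.52 to 3.85
- 20% vs 5%: SE = √(1/10.06 + 1/24.94 + 1/14 + 1/21) = 0.508, 95% CI about 0.61 to 4.48

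The chance of two-sided *p* < 0.05 is roughly 10% and 17%.

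**Wider range of assumptions.** With *a* equal in both arms at 0.20, 0.30 or 0.40, and deaths of 20 vs 10, 25 vs 10, 30 vs 15, 30 vs 10 or 40 vs 10 per cent, the odds ratio (fewer deaths against more) lies between 0.36 and 0.79. At *a* = 0.30:

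| Deaths among AKI-free patients | Recorded stage 3 AKI | OR |
|---|---|---|
| 20% vs 10% | 44.0% vs 37.0% | 0.75 |
| 30% vs 10% | 51.0% vs 37.0% | 0.56 |
| 40% vs 10% | 58.0% vs 37.0% | 0.43 |

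Over the whole range, the chance of significance from deaths alone is about 7% to 28% for gaps of 10 to 20 points, and 33% to 54% for a 30-point gap.

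**In counts.** Ten true cases in each arm plus 2 vs 10 other deaths give 12/35 vs 20/35. OR = (12 × 15)/(23 × 20) = 0.39, 95% CI 0.15 to 1.03.

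**Masking.** Suppose true AKI is 20% vs 30%, a true OR of (0.20/0.80)/(0.30/0.70) = 0.58, with deaths among AKI-free patients of 30% and 20% respectively. The recorded risks are 0.20 + 0.80 × 0.30 = 0.44 and 0.30 + 0.70 × 0.20 = 0.44, an OR of 1.00. The renal difference disappears.

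**The case against.** The rule is openly prespecified in the Outcomes section, and it is a legitimate way to handle death. Death before D7 truncates the renal outcome, and scoring it as unfavourable keeps every randomised patient in the intention-to-treat comparison. Both points stand. A reader might infer a concealed composite, but the documents do not support that: only the name and definition fail to match the rule.

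A reader might also infer that deaths at any time up to day 28 count, because the sentence itself sets no limit. The D7 default in the same section and the abstract's wording about earlier events confine it to deaths by D7. Nor is it a fault that these deaths also enter 28-day survival. The two are separate outcomes with different windows, nothing adds them together, and showing mortality beside a composite that contains it is good practice.

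A component table is commonly left to an analysis plan, so its absence here is not the finding. The finding is that the article fixes both a renal label and a counting rule that contradicts it. Other planned outcomes help only in part. Creatinine and clearance receive assigned values on death under the same rule, so they do not isolate the kidney either. RRT-free days do separate death, but cover RRT only.

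The magnitude rests on assumed death imbalances, and at this sample size the illustrated shifts lie well within sampling error. The exclusions for uncontrolled bleeding, refractory shock, extreme severity and futility remove some early non-renal deaths, though not later ones. The article itself concedes limited power for some secondary outcomes. All of this stands and limits the weight of the point.

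**Conclusion.** The point holds as a mislabelled secondary outcome. What will be analysed is stage 3 AKI, RRT or all-cause death by D7, and the plan reports its odds ratio as an AKI result. With equal true AKI of 25% and deaths among AKI-free patients of 5% vs 15% to 20%, the odds ratio moves from 1.0 to between 1.41 and 1.65, and the same mechanism can hide a real difference. These rates are illustrative, since the documents supply none.

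A reader might infer that the trial is likely to declare a false renal effect. The working does not support that: with 35 per arm, a significant result from deaths alone would usually need a large mortality gap. The distortion lies in the estimate and its interpretation. The primary outcome's sample size is untouched.

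**What to change.** Keep the composite, but name it stage 3 AKI, RRT or death by D7 wherever it appears, and write the D7 limit into the counting rule. Report each component by arm beside the composite odds ratio. Base any statement about AKI on a separate analysis of KDIGO stage 3 AKI or RRT, with death before D7 as its own competing category, in line with the treatment already planned for RRT-free days.

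The cost is a change of wording, one table and one further analysis. The data are already collected: serum creatinine and urine output up to D7, RRT days, and deaths. The drawback is that the AKI-only comparison has fewer events and a wider interval.

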#### Exclusion criteria

Exclusion criteria are defined by the following:Extreme age (≥ over 75 years old),Acute surgical condition or laparotomy in the preceding 4 weeks,Previous liver transplant,Hemorrhagic ascites (red blood cells count > 10,000/mL) [16],Extreme clinical severity (APACHE II ≥ 34),Any of the following conditions present 24 h after admission:aHemorrhagic shock with active uncontrolled bleeding,bRefractory shock (mean arterial pressure < 65 mmHg) despite multiple vasopressor support,Predictably short (< 72 h) ICU stay andTherapeutic futility determined by the medical staff.

Notes:These criteria are to be applied independently of any previous treatments of ascites, including recent LVP (i.e., in the emergency department before ICU admission), andExamples of “predictably short (< 72 h) ICU stay, precluding patient enrolment, may be, i.e., the reversal of clinical instability after initial therapy and adequate resuscitation in the ICU, such as < 6 h of vasopressor support; variceal bleeding controlled in the ICU without developing organ failure; or prompt reversal of oliguria/AKI.

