## Assignment of interventions: allocation

### Sequence generation {16a}

The patient allocation method consists of stratified randomization with blocks within each subgroup. This method is particularly useful with randomizing small samples due to the ability to create balanced groups regarding predetermined variables or characteristics at the beginning of the trial, reducing differences in baseline trial groups characteristics’ that could harm later result analysis and conclusions.

In this small sample size trial, patients will be stratified according to maximum serum creatinine and maximum IAP, expected to be the two most important variables to balance between trial groups at baseline. Stratified randomization will homogenize trial groups ad initio to reduce the probability of unbalanced baseline group characteristics and biased results.

The stratification process will use two strata, namely, maximum IAP and maximum serum creatinine, thus creating four subgroups (I–IV): (I) IAP < 16 mmHg + serum creatinine < 1.5 mg/dL, (II) IAP < 16 mmHg + serum creatinine ≥ 1.5 mg/dL, (III) IAP ≥ 16 mmHg + serum creatinine < 1.5 mg/dL, and (IV) IAP ≥ 16 mmHg + serum creatinine ≥ 1.5 mg/dL [4, 13]. Each subgroup (I–IV) contains sequential blocks of randomized trial group allocation (A) control and (B) intervention, with a 1:1 ratio (i.e., *AABB*, *ABAB*, *BABA*, *BBAA*), as exemplified in Table 1.

**Table 1 Tab1:** Stratification subgroups (I-IV) created using maximum intra-abdominal pressure (IAP) and serum creatinine as strata. Example of stratified randomization with blocks within each subgroup (A, B)

Stratification subgroups (I–IV)	Creatinine < 1.5 mg/dL	Creatinine ≥ 1.5 mg/dL
IAP < 16 mmHg	I) ABAB, ABBA,…	III) BABA, BBAA,…
IAP ≥ 16 mmHg	II) BABA, AABB,…	IV) BBAA, BAAB,…

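### A flat 4 mg/dL score for RRT or death can rank those patients better than living, RRT-free patients whose day-7 creatinine is above 4 mg/dL

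*Protocol article*

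**What the plan says.** In the protocol article, Outcomes {12} states "The primary outcome is serum creatinine concentration" and sets the time point: "The outcomes variables will be assessed at day seven (D7) after randomization (D0), unless otherwise stated". Two substitution rules follow.

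- RRT or death: the patient is counted as a stage 3 AKI case, and the scores are fixed: "a serum creatinine concentration value of 4 mg/dL and creatinine clearance value of 10 mL/min will be used".
- Early discharge or transplant: "Whenever ICU discharge or liver transplant occurs before D7, the last available data prior to these events will be used for outcome assessment".

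The second rule has no cap, and no cap is stated for measured day-7 values. The list under Exclusion criteria ("Exclusion criteria are defined by the following") contains neither a creatinine ceiling nor RRT at entry. The high-creatinine strata in Sequence generation {16a} are open-ended, for example "IV) IAP ≥ 16 mmHg + serum creatinine ≥ 1.5 mg/dL". The scored values are then compared under Statistical methods {20a}: "Mann–Whitney *U* test will be used to compare study groups, assuming a non-normal distribution, or two independent sample *t*-test, in case of normal distribution".

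**The concern.** The rule is meant to make RRT and death a bad result. It does so only for patients whose creatinine would otherwise be below 4 mg/dL. Above that level, the score assigned to RRT or death is lower, and so better, than the value kept by a patient who stays alive without RRT. Two patients at 5.0 mg/dL show it: the one discharged before day 7 scores 5.0 and the one who dies scores 4.0.

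Clearance has the mirror-image fault. A dead patient is given 10 mL/min, which is better than a living patient with a measured clearance below 10.

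If such events were more common in one arm, the primary comparison could move towards that arm. The protocol also allows the trial to stop after 30 patients on a significant primary-outcome difference, when each arm is small. The trial is open label, so the RRT decision that triggers the score is taken with allocation known.

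**Working it through.** **1. The plan's own sample size, as a reference.** Sample size {14} gives 0.9 ± 0.45 and 1.3 ± 0.48 mg/dL, a difference of 0.4, one-sided alpha 0.05 and 95% power. Pooled SD = √((0.45² + 0.48²)/2) = 0.465. The noncentral t gives 30 per arm, 60 in total, with power 0.950. This reproduces the stated 60. For 15% attrition, 60/0.85 = 71 and 60 × 1.15 = 69, consistent with 70. The scoring point does not alter these figures.

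**2. Ordering.** For a living patient at c mg/dL and a patient with RRT or death scored 4, the second ranks better whenever c > 4. This follows from the text alone. At c = 5.0 the gap is 4.0 − 5.0 = −1.0 mg/dL.

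**3. Mean scale, assumed case.** Let 3 of 30 patients in each arm (10%, assumed) be at 5.0 mg/dL. In one arm all three get RRT or die; in the other they live without RRT; everyone else is below 4 and identical. The arm with the events has a mean lower by 3 × 1.0/30 = 0.10 mg/dL, and 0.10/0.4 = 25% of the target. At the interim, with about 15 per arm, two such patients give 2 × 1.0/15 = 0.13 mg/dL, a third of the target.

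**4. Rank scale, same case as the 30-per-arm example.** Only 3 × 3 = 9 of 30 × 30 = 900 pairs change, each from a tie to a win. The Mann–Whitney probability moves from 0.500 to 0.500 − 0.5 × 9/900 = 0.495. The planned effect is 0.4/0.465 = 0.86 SD, which under normality is Φ(0.86/√2) − 0.5 = 0.23. The distortion is 0.005/0.23, about 2% of the planned effect. Worst-rank scoring would give 0.505, so against that benchmark it is 0.010/0.23, about 4%.

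**5. A heavier case.** Take 35 per arm, with k patients per arm at 5.5 mg/dL (assumed): event-free in control, RRT or death in the intervention arm. For k = 2, 4 and 6 the mean difference is −1.5k/35 = −0.09, −0.17 and −0.26 mg/dL, favouring the arm with the events. If the events were scored 6.0, worse than every measured value, it would be +0.5k/35 = +0.03, +0.06 and +0.09. For k = 6 the Mann–Whitney probability is 0.485 with the flat 4 and 0.515 with worst-rank scoring.

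**6. Simulation.** 35 per arm, the same lognormal creatinine in both arms (log-SD 0.6, assumed), 4,000 replicates. Every intervention patient above 4 is converted to RRT or death and no control patient is, which is deliberately extreme.

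| Assumed median (mg/dL) | Share above 4 | Mean difference, flat 4 | One-sided Mann–Whitney 'benefit', flat 4 | Same, worst rank |
|---|---|---|---|---|
| 1.5 | 5% | −0.07 | 5.3% | 5.0% |
| 2.0 | 12% | −0.20 | 6.0% | 3.9% |
| 2.5 | 22% | −0.41 | 9.3% | 2.4% |

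Converting only half of them roughly halves the mean shifts and gives flat-4 rates of 5.3%, 5.6% and 7.3%. The simulation error on a 5% rate is about 0.3 percentage points, so the first row shows no detectable effect on the test.

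**7. How common are values above 4?** Under the planning figures, below 0.05% even if lognormal. Those figures do not describe the strata at 1.5 mg/dL and above that the trial enrols, and the document gives no others.

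**The case against.** The strongest reply is that this is an edge case. Below 4 mg/dL the rule correctly penalises RRT and death. The planning figures imply almost no patients above 4. The named test for non-normal data is Mann–Whitney, which barely reacts to a few reordered patients. A shift between arms needs the events to differ by arm among patients above 4, and stratification at 1.5 mg/dL limits baseline imbalance. RRT and death also appear in stage 3 AKI, RRT-free days and 28-day survival, and a data monitoring committee looks for harm.

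Most of this stands as a limit on size. It does not rescue the ordering, which is wrong as written, and the secondary outcomes do not repair the primary score.

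A reader might infer more than the text supports:

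- That the primary outcome records death as an improvement of 1.0 mg/dL. It does not: the endpoint is the day-7 value, not a change from baseline.
- That the bias is a quarter of the target effect. That is a shift in means under an assumed 10% share and wholly one-sided events. In the same case the rank test moves by about 2%.
- That patients already on RRT at D0 show the same reversal. Those who stay on it score 4 in both arms. This may dilute the contrast, but it is symmetric and a separate matter.

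**Conclusion.** The point holds as a fault in a stated rule. Above 4 mg/dL (or below 10 mL/min clearance), RRT or death is scored better than survival without RRT, and the eligibility criteria do not keep such patients out. That conclusion needs no assumption.

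Its effect on the result cannot be fixed from the document. Under the Mann–Whitney test it is small if few patients exceed 4 mg/dL and the events are balanced between arms. It becomes material if many exceed 4 and the events differ by arm, and it is larger for the t-test, mean summaries and mixed models. The numerical illustrations rest on assumed shares, assumed creatinine values and one-sided events. The claim that the treatment contrast is in fact biased is not supported. This should be fixed before any comparative analysis, including the interim at 30 patients.

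**What to change.** - **Primary comparison:** keep RRT and death as the worst category, as the rule intends. Commit to Mann–Whitney for day-7 creatinine and rank these patients worse than every measured value. Do the same for clearance.
- **Mean-scale summaries and mixed models:** score RRT or death as the higher of 4 mg/dL and the last creatinine measured before the event. For clearance, use the lower of 10 mL/min and the last pre-event value. This only partly cures the ordering, since a patient who dies at 4.5 still scores better than a living patient at 5.5. It should therefore support the rank analysis and not replace it.
- **Sensitivity analyses:** report the flat-4 version, and one restricted to patients who at D0 were not on RRT and had creatinine below 4 mg/dL. That subset is defined on D0 status, so it keeps the randomised comparison provided the values used predate allocation.

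The cost is a change of analysis wording, with no effect on eligibility, data collection or care. The main result becomes rank-based, with the mg/dL difference as supportive, so it corresponds less directly to the 0.4 mg/dL used for the sample size. The flat 4 already merges RRT and death into the score, so the outcome is a composite either way.
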